### Vigorous-intensity exercise adherence prescription integrity

2.14

Vigorous Intensity Exercise Adherence. Participant adherence in the integrated study arm will be assessed with the daily REDCap surveys and with the Apple Watch heartrate data. Participants will be asked to enter the type of physical activity and number of minutes exercised, average heartrate, and perceived exertion into the daily REDCap exercise adherence survey. For the individuals in the PACE condition who fail to complete the prescribed weekly dose, brief reminder calls will be made by the research staff. The calls are designed to: (1) foster motivation and impetus for behavioral change, and (2) troubleshoot potential barriers to physical activity.

Heart rate will be monitored with the Apple Watch. Participants will be asked to wear the Apple Watch every day as well as for each session of exercise. The watch will monitor the level of heart rate and provide the average heart rate for the session. Participants will be asked to enter this information on the daily REDCap survey. In addition, Status/Post will pull the heart rate data from HealthKit on the Apple Watch and mobile device, allowing us to verify transcribed data. A participant will meet the weekly prescription if they have evidenced at least 75 min of at least 76% of maximum heart rate.

### Team RWB prescription integrity

2.15

Participant adherence will be assessed using the daily REDCap adherence surveys. For the individuals in the PACE group who failed to attend a weekly event, brief reminder calls will be made by the research staff. The calls are designed to: (1) foster motivation and impetus for behavioral change, and (2) troubleshoot potential barriers to community engagement. Researchers will use the call as an opportunity to encourage the participant to attend at least one event the following week. Research staff will not schedule reminder calls for those in the Team RWB alone arm in order to ensure that this group is a pure test of the current organization and procedures.

### Acceptability

2.16

Acceptability Interview. This measure will assess participants' perceptions of the PACE program in terms of likelihood of future engagement, program likeability, and perceived benefits of the intervention (e.g., “Some people feel like other things going on in their lives have impacted their experience in this program. What, if any, things in your life outside of the program impacted your experience?” or “What did you like or find helpful about the PACE program; what benefits have you noticed?”) The measure will be administered at follow-up online via REDCap.

## Data analysis

3

As the project is designed to be a proof-of-concept, the primary aim is to gather information about acceptability as well as initial effect sizes of the PACE program. In this way, the data can help to guide treatment development and inform future efficacy studies. In order to examine the acceptability of the PACE program, we will report on intervention adherence (e.g., vigorous-intensity exercise adherence, Team RWB attendance) as well as items from the acceptability interview.

We will initially examine baseline differences between groups on various demographic and psychological variables (e.g., military rank, gender, reintegration difficulties) to ensure that there are no prior differences between groups. Any variables on which the groups differ will be used as covariates in subsequent analyses. Effect sizes of PACE relative to WL or RWB only, respectively, will be estimated using [7] adaptation of Cohen's *d* to mixed effects models. Effect size analyses will be complemented by traditional significance testing employing repeated ANCOVA using mixed effects models with the M2C-Q as the dependent variable, time as the within-subjects variable and intervention group (Team RWB + Vigorous-Intensity Exercise, Team RWB, WL) as the between-subjects variable.

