### Study design

2.1

Sixty veterans discharged from the U.S. military will be randomly assigned to: 1) PACE, which includes vigorous-intensity exercise counseling and monitoring in addition to participation in a community-based program (Team RWB) or (2) 8 participation in Team RWB alone or (3) waitlist. The project will be a collaboration between the University of Texas at Austin (UT) and Team RWB. UT Austin will conduct all research activities and refer participants to Team RWB activities. The primary outcome – community reintegration difficulties - will be assessed at baseline, biweekly during the intervention period, and after 8 weeks of the intervention. PACE and Team RWB aim to aid the development of long-term habits and thus are not time-limited, Hence, the current study will report on the early effects of these programs – i.e., bi-weekly during the first 8 weeks and 1-week following 8 weeks of participation.

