#### Follow-up

2.8.4

Participants will be asked to complete a final assessment on REDCap one week following study completion (i.e., week 9), which will serve as the major endpoint for initial efficacy. Participants who met the survey requirements (i.e., follow up and at least 2 of the biweekly assessments) will keep the Apple watch. Those who do not will be asked to return the Apple Watch within two weeks of the week 9 follow-up.

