### Randomization

2.9

The principal investigator will oversee the randomization. Randomization will be stratified by military rank (i.e., officer or enlisted status). Variable-sized permuted block randomization will be completed using Sealed Envelope to assign individuals to treatment condition (Sealed Envelope Ltd. 2016).

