### Power analyses

3.1

The primary objective during this developmental phase is to estimate the effect size of the PACE program. Thus, we recognize that the study is not powered to detect small statistical differences between the three groups. A post hoc power analysis (power = 0.8, α = 0.05) indicated that the final model, with the sample size of 60 participants, allowed us to detect a significant medium effect size of *f*^*2*^ = 0.25 for the between by within subject interaction.

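### Covariates enter the model only if the groups are seen to differ at baseline, so adjustment for baseline M2C-Q and the stratification factor is left to chance

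*Protocol article*

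**What the plan says.** The Data analysis section of the protocol article starts with a comparison of the arms at baseline on demographic and psychological variables ("e.g., military rank, gender, reintegration difficulties"). Its stated purpose is "to ensure that there are no prior differences between groups". The rule follows: "Any variables on which the groups differ will be used as covariates in subsequent analyses". No test, significance level or size of difference is attached to it.

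The main model is a repeated ANCOVA fitted as a mixed model, "with the M2C-Q as the dependent variable, time as the within-subjects variable and intervention group" as the between-subjects variable. No covariate is fixed in advance.

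Three other places bear on this:

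- Randomization: "Randomization will be stratified by military rank (i.e., officer or enlisted status".
- Study design: the primary outcome "will be assessed at baseline, biweekly during the intervention period, and after 8 weeks of the intervention".
- Follow-up: the final assessment is "one week following study completion (i.e., week 9), which will serve as the major endpoint for initial efficacy".

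The text does not say whether the baseline M2C-Q is one of the levels of time in the outcome.

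**The concern.** When allocation is random, any baseline difference between arms is chance. Its size does not show whether the variable predicts the outcome, and prediction is what makes a covariate worth including. The rule selects on the wrong property, with three consequences.

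- **Baseline M2C-Q**, plausibly the best single predictor of later M2C-Q, is adjusted for only when it happens to be visibly imbalanced.
- **Military rank** is balanced through stratified blocks, so it will rarely look different and will usually be left out, although the randomisation used it.
- **The final model** is unknown until the data are seen. With no definition of differing, the choice rests with the analyst.

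The main product of this pilot is an effect size for planning a larger trial. That estimate would be less precise than the data allow, and in some trials it would carry a chance imbalance that the plan could easily have removed.

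**Working it through.** **Inputs.** From the documents: 60 participants in three arms, stratification by rank, major endpoint at week 9. Assumed, because not given: 20 per arm, differing means p < 0.05, correlation ρ between baseline and week-9 M2C-Q of 0.3, 0.5 or 0.7, equal SDs at both times, one follow-up time, no dropout. The one figure in Power analyses (f² = 0.25 with 60 participants) does not bear on the covariate rule. It also cannot be settled from the text, which omits the number of time points, the correlation and the effect-size convention.

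**1. How often the rule acts.** By construction, a 5% test flags baseline M2C-Q in about 5% of randomised trials. If 10 independent variables were examined, at least one would be flagged by chance with probability 1 − 0.95^10 = 0.40.

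**2. Precision.** With outcome SD 1, the variance factors are 1 for an unadjusted post-baseline comparison, 2(1 − ρ) for change from baseline, and 1 − ρ² for ANCOVA. So always adjusting multiplies the variance by 1 − ρ² against the first, and by (1 − ρ²)/[2(1 − ρ)] = (1 + ρ)/2 against the second.

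| ρ | against unadjusted | against change | unadjusted N matching 60 adjusted: 60/(1 − ρ²) |
|---|---|---|---|
| 0.3 | 0.91 | 0.65 | 66 |
| 0.5 | 0.75 | 0.75 | 80 |
| 0.7 | 0.51 | 0.85 | 118 |

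These are large-sample ratios. At ρ = 0.7, simulated SDs were 0.2283 (always adjusted), 0.3151 (unadjusted) and 0.2454 (change), giving (0.2283/0.3151)² = 0.52 and (0.2283/0.2454)² = 0.87, close to the formula.

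Simulated power for one pairwise contrast at an illustrative d = 0.8 (40,000 trials per setting), rule against always adjusting:

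| ρ | outcome is post-baseline only | baseline is a level of time (change) |
|---|---|---|
| 0.3 | 0.71 vs 0.73 | 0.57 vs 0.73 |
| 0.5 | 0.71 vs 0.81 | 0.71 vs 0.81 |
| 0.7 | 0.72 vs 0.93 | 0.90 vs 0.93 |

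**3. Imbalance that the rule misses.** The difference in baseline means between two arms of 20 has SD √(2/20) = 0.316. A difference beyond ±0.4 SD therefore lies beyond 0.4/0.316 = 1.265 standard errors, with probability about 0.21. In simulation, about 83% of these trials were not flagged by the three-arm test.

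Given a PACE-waitlist difference above +0.4 SD, its mean is 0.316 × 0.179/0.103 = 0.55 SD. With no adjustment, the week-9 comparison carries ρ × 0.55 = 0.17, 0.28 or 0.39 SD. Under the rule, which rescues the flagged trials, the simulated mean error was 0.13, 0.22 and 0.30 SD. Always adjusting leaves about 0. With change from baseline, the error has the opposite sign and is proportional to 1 − ρ instead of ρ. Its size therefore mirrors these values, about 0.31, 0.22 and 0.13 SD, if flagged trials switch to ANCOVA.

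**4. If baseline is both a level of time and a covariate.** A main-effect covariate is constant within a person, so it cannot move a within-person contrast. In one simulated complete data set (3 × 20, six times, ρ = 0.5, no true effect), the group-by-week-9 term was −0.1035 with and without the covariate; post-baseline ANCOVA gave 0.004. With 15% of post-baseline values missing, it was −0.111 without and −0.106 with it.

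**5. Type I error under the rule.** Simulated with a post-baseline outcome: 0.048, 0.046 and 0.041 at ρ = 0.3, 0.5 and 0.7.

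**The case against.** The best defence is that this is a proof-of-concept study. Its aims are acceptability and initial effect sizes, and significance tests only complement them. Randomisation keeps the unadjusted estimate unbiased on average, and type I error under the rule is at or slightly below 5%. The loss can also be small: 0.71 against 0.73 power at ρ = 0.3 with a post-baseline outcome, or 0.90 against 0.93 at ρ = 0.7 with change. The entry threshold of 1.5 on the M2C-Q may restrict the baseline range and lower ρ. All of this stands, and it limits the severity. It does not defend the rule, because some precision is lost at every ρ considered and under either model.

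A reader might infer three stronger points that the documents do not support.

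- **That the rule never corrects the imbalance it targets.** If the outcome is post-baseline only, adding a flagged variable does adjust for it. The correction fails only if baseline is also a level of time, which the text leaves open.
- **That covariates are chosen by a 5% test.** The text speaks only of examining differences. The 5% and 40% figures illustrate one reading. Without a test, the choice is more discretionary.
- **That leaving out rank costs a known amount.** Nothing in the article says how prognostic rank is.

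An unseen analysis plan does not answer the point, because the article states this rule and is not merely silent.

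**Conclusion.** The point holds as a matter of precision and pre-specification. Covariate choice depends on chance differences, with no criterion, and covers the two variables with the clearest claim to a fixed place: baseline M2C-Q and rank. Always adjusting for baseline would lower the variance of the week-9 contrast by 9% to 49% against an unadjusted comparison, or by 15% to 35% against change from baseline. In about one trial in five, a PACE-waitlist imbalance above 0.4 SD arises. It usually goes unadjusted and leaves a mean error of about 0.13 to 0.31 SD in the estimate meant to inform the follow-up trial.

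These sizes rest on 20 per arm, ρ between 0.3 and 0.7, a 5% cut-off and a single follow-up time. How imbalance enters the effect-size method that the article cites was not checked, since that source is not available. It would be wrong to conclude that the trial is biased or its error rate inflated. This should be fixed, but it does not stand in the way of the pilot.

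**What to change.** Replace the rule with a model fixed in advance:

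- Use the post-baseline M2C-Q values as outcome, with baseline M2C-Q, its interaction with time, and rank stratum as fixed covariates. A longitudinal model with baseline means constrained equal across arms, plus rank, serves the same purpose. Either choice also settles whether baseline is a level of time.
- Treat secondary outcomes likewise where everyone has a baseline value. The PCL-5 is an exception, because it is given only to those scoring 3 or more on the PC-PTSD-5.
- Report baseline characteristics descriptively and do not use them to select covariates.

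The cost is about two sentences of text and, at the week-9 contrast, about two degrees of freedom (one for baseline, one for rank). No new data are needed, because baseline M2C-Q and rank are already collected.

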### Specific aims

2.2

1. To assess, in a randomized clinical trial, the feasibility and acceptability of the PACE program. We will examine participant attendance to prescribed activities as well as participant satisfaction with the program using an acceptability interview following study completion.

2. To evaluate the effectiveness of the PACE program on the level of reintegration difficulties on the following primary outcome measure: Military to Civilian Questionnaire (M2C-Q; [20].

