#### Team RWB

2.8.1

Participants assigned to the Team RWB arm will be prescribed 1 Team RWB event per week for the 8-week duration of the study. Participants will be guided through the process of joining Team RWB. Research staff will have the participant “Join the Team” on the organization's site: https://www.teamrwb.org/join/. Research staff will connect the participant via email to the correct chapter representative based on which chapter the participant expresses interest in. In this way, research staff can ensure that the participant is connected with the organization in a timely manner. Participants will receive a monthly calendar of Team RWB events upon assignment. They will be asked to attend at least one Team RWB event. This could be a weekly running group, social event, or community service project, among other activities. We did not discourage the use of exercise in this arm in order to optimize the ecological validity of the program.

Participants assigned to this condition will also enter whether or not they attended a Team RWB event on the daily automated REDCap surveys. Participants will be asked to not initiate an exercise program outside of the context of Team RWB for the duration of the study. However, if they do become involved in another fitness program, we will ask that they report this to study staff. The staff will save this information as a note to file and these data will be reported in the outcome report. In order to be able to evaluate the effects of Team RWB as it is administered, research staff will not provide any guidance to participants or participate in trouble-shooting non-adherence.

Study staff will schedule a total of four online surveys to be distributed via REDCap every two weeks. The surveys should take approximately 30 min to complete and participants will be compensated $20 per assessment.

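### Week 9 is the major efficacy endpoint and Aim 2 concerns PACE, but the only significance test stated is an omnibus group-by-time test that isolates neither

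*Protocol article*

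**What the plan says.** All references are to the protocol article.

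- Section 2.2, Aim 2: "To evaluate the effectiveness of the PACE program on the level of reintegration difficulties", measured by the M2C-Q.
- Section 2.8.4 (Follow-up): the final assessment is one week after the 8-week period ("i.e., week 9), which will serve as the major endpoint for initial efficacy").
- Section 2.1 (Study design): the M2C-Q "will be assessed at baseline, biweekly during the intervention period, and after 8 weeks of the intervention", and early effects are reported "bi-weekly during the first 8 weeks and 1-week following 8 weeks of participation". Section 2.8.1 (Team RWB) specifies "a total of four online surveys to be distributed via REDCap every two weeks".
- Section 3 (Data analysis): the leading analysis is a Cohen's d, adapted to mixed models, for PACE against waitlist and against Team RWB. Significance testing complements it, through a mixed-model repeated ANCOVA "with the M2C-Q as the dependent variable, time as the within-subjects variable and intervention group", where group has three levels.
- Section 3.1 (Power analyses): the detectable effect is given "for the between by within subject interaction".

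The article names no significance test at week 9 and none of PACE against either comparator. It does not say which occasion the effect sizes refer to.

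**The concern.** The endpoint is one occasion and the aim concerns one arm against its comparators. The stated test pools three arms and every occasion. It responds to any departure from parallel profiles: Team RWB alone improving, both active arms improving equally, or a brief mid-study difference that has gone by week 9. None of these says that PACE reduces reintegration difficulty at the endpoint.

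The comparison most exposed is PACE against Team RWB. The introduction justifies PACE by what exercise counseling and monitoring might add to Team RWB. A significant interaction could be read as support for PACE when that addition is nil. The discussion expects the effect sizes to supply data for a large follow-up trial, so the occasion they refer to also matters.

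**Working it through.** **The plan's own figure.** Section 3.1 gives f² = 0.25 at 80% power, α = 0.05, N = 60. It cannot be reproduced or refuted, because the number of occasions, the within-subject correlation and any sphericity correction are not stated. The point does not depend on it. What matters is that it names the interaction as the powered effect.

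**Inputs from the article.** Three arms; 60 participants; baseline, four biweekly surveys and week 9, so six occasions. The count is inferred from Sections 2.1, 2.8.1 and 2.8.4, taking the survey schedule stated under Team RWB to hold for all arms.

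**Assumptions, not in the article.** 20 per arm, no dropout, compound symmetry with correlation ρ = 0.5, unit SD, time categorical, occasions at weeks 0, 2, 4, 6, 8 and 9.

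**Degrees of freedom.** Numerator (3 − 1) × (6 − 1) = 10; denominator (60 − 3) × (6 − 1) = 285. The 5% critical F is 1.864. The noncentrality is λ = n × S / (1 − ρ), where S is the sum of squared interaction deviations of the cell means.

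**Scenario A: PACE equals Team RWB; both diverge linearly from waitlist to 1.0 SD at week 9.**
- Time part: weeks have sum of squares 201 − 29²/6 = 60.83; divided by 9² this is 0.7510.
- Group part: values 1, 1, 0 have sum of squares 2/3.
- S = 0.7510 × 2/3 = 0.5007; λ = 20 × 0.5007 / 0.5 = 20.03.
- Rejection probability: **88%**, although PACE minus Team RWB is zero at every occasion.

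**Scenario B: one arm differs by 0.8 SD at week 2 only.**
- Time part: 0.64 × (1 − 1/6) = 0.5333. Group part: 2/3.
- S = 0.3556; λ = 20 × 0.3556 / 0.5 = 14.22.
- Rejection probability: **71%**, although no arms differ at week 9.

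**Sensitivity to ρ.** At ρ = 0.3, A is 72% and B is 53%. At ρ = 0.7, A is 99% and B is 93%.

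**Sensitivity to time coding.** With linear time the interaction has 2 df. Scenario A keeps λ = 20.03, because its profile is linear; on 2 and 57 df it rejects 98% of the time. Linear coding therefore does not separate PACE from Team RWB.

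**Power of interaction and contrast (ρ = 0.5, linear divergence).**

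| Week-9 benefit of PACE | Interaction, 10 df | Interaction, linear time, 2 df | Contrast with waitlist, baseline-adjusted | Contrast with waitlist, change from baseline | Same, α = 0.025 |
|---|---|---|---|---|---|
| 0.8 SD over both arms | 66% | 89% | 82% | 70% | 59% |
| 0.5 SD over both arms | 26% | 48% | 43% | 34% | 24% |
| 0.8 SD over waitlist, 0.4 SD over Team RWB | 51% | 78% | 82% | 70% | 59% |

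The contrast standard errors are √(2(1 − 0.5²)/20) = 0.274 (baseline-adjusted, 56 df) and √(4(1 − 0.5)/20) = 0.316 (change from baseline, 57 df). In the last row the other contrast, PACE against Team RWB at 0.4 SD, has about 30% power with baseline adjustment. The ordering of interaction and contrast changes across the columns.

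**The case against.** The strongest reply is that the significance test is not the main analysis. Sections 3 and 3.1 say the trial exists to estimate effect sizes, and Section 3 already plans PACE against waitlist and PACE against Team RWB. In Scenario A the PACE-versus-RWB d would be expected near zero and would be reported beside the F test. Section 3.1 also disclaims power for small differences. This stands, and it limits the severity. A reader might infer that the plan never compares PACE with its comparators; that is wrong. What the planned d lacks is a link to week 9 and an interval or test.

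A second reply concerns power. A reader might infer that the omnibus test wastes power by spreading over 10 df. The article does not support this. It does not say whether time is categorical, and linear time gives 2 df. Comparing a change-from-baseline interaction with a baseline-adjusted contrast is also not like for like. On equal terms the 0.8 SD figures are 66% and 70%, and splitting α puts the contrast below the interaction. If effects are immediate and correlation decays, the interaction can win clearly. That objection is accepted in full.

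A third reply is that follow-up contrasts are commonly left to a fuller document. In part they are. But the article itself states the endpoint, the model and the powered effect, and these do not line up.

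**Conclusion.** The point holds as a mismatch between the hypothesis tested and the question asked. Week 9 and PACE define the efficacy question, while the stated and powered test is an omnibus interaction over three arms and all occasions. The 88% and 71% rest on 20 per arm, compound symmetry, ρ = 0.5, categorical time and no dropout. The logical point needs none of these: a significant interaction is compatible with no PACE effect at week 9 under any coding of time.

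The defect is modest. This is a pilot whose leading analysis is estimation, and the right pairs of arms are already named. The case for change is that inference should address the aim, not that it gains power.

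**What to change.** State in Section 3 that inference for Aim 2 consists of the model-based week-9 M2C-Q differences PACE minus waitlist and PACE minus Team RWB, each with a 95% CI, and that the reported d is derived from these same contrasts. Fit time as categorical so that week 9 is estimated directly. Describe the group-by-time interaction as supportive.

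This costs one or two sentences and uses the same data and mixed-model framework. Two drawbacks should be stated. There are two comparisons instead of one, so the plan should say whether α is split. Precision for PACE against Team RWB is also low: with ρ = 0.5 and baseline adjustment, power for 0.4 SD is about 30%, and the 95% CI half-width is about 2.003 × 0.274 = 0.55 SD.
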